## Abstract

**Introduction:**

The healthcare and well-being of the population depend on multiple factors and should adapt to societal changes. The opposite is also occurring; society has evolved concerning the individuals’ approach to their care, which includes participation in decision-making processes. In this scenario, health promotion and prevention become crucial to provide an integrated perspective in the organization and management of the health systems.

Health status and well-being depend on many aspects, determinants of health, which in turn may be modulated by individual behavior. Certain models and frameworks try to study the determinants of health and individual human behaviors, separately. However, the interrelation between these two aspects has not been examined in our population.

Our main objective is to analyze whether personal aptitudes related to behaviors are independently associated with the incidence of morbidity. A secondary objective will enquire whether these personal aptitudes are independently associated with lower all-cause mortality, enhanced adoption of healthy lifestyles, higher quality of life, and lower utilization of health services during follow-up.

**Methods:**

This protocol addresses the quantitative branch of a multicenter project (10 teams) for the creation of a cohort of at least 3,083 persons aged 35 to 74 years from 9 Autonomous Communities (AACC). The personal variables to evaluate are self-efficacy, activation, health literacy, resilience, locus of control, and personality traits. Socio-demographic covariates and social capital will be recorded. A physical examination, blood analysis, and cognitive evaluation will be carried out.

Several sets of six Cox models (one for each independent variable) will analyze the incidence of morbidity (objective 1); all-cause mortality and the rest of the dependent variables (objective 2). The models will be adjusted for the indicated covariates, and random effects will estimate Potential heterogeneity between AACC.

**Discussion:**

The analysis of the association of certain behavioral patterns and determinants of health is essential and will contribute to improving health promotion and prevention strategies. The description of the individual elements and interrelated aspects that modulate the onset and persistence of diseases will allow the evaluation of their role as prognostic factors and contribute to the development of patient-tailored preventive measures and healthcare.

**Clinical Trial Registration**: ClinicalTrials.gov, NCT04386135. Registered on April 30, 2020.

## Introduction

1.

In Spain, the population over 65 years of age is expected to increase by 10% in the next 50 years (1); and the total dependency ratio to grow from the current 54.2 to 72.2%. The aging of the population is associated with an increase in the number of people with chronic diseases (osteoarticular, cardiovascular, respiratory, mental, neurodegenerative, and cancer) and the resulting higher multimorbidity (two or more concurrent conditions) (2). This poses a great challenge to the health systems because the demand for health and social services escalates (3).

Chronic diseases are the leading cause of overall mortality and premature mortality in the world (they are related to 42% of the deaths occurring before 70 years of age). These conditions have an enormous impact on people’s daily life and their families, and represent a heavy burden on society (4). Among chronic diseases, the high prevalence of mental disorders is worth mentioning (5). Major depression, specifically, holds second place worldwide in terms of disability and disease burden (6). Mortality rates in people with mental health problems are up to double those in people without them. But importantly, most chronic diseases and their complications could be prevented through health promotion and primary prevention strategies; approximately 80% of cardiovascular diseases and 30% of all cancers could be averted (4).

Health promotion and prevention interventions play an essential role when considering the wellbeing of the population from a comprehensive perspective. According to the World Health Organization (WHO), health is a state of physical, mental, and social well-being that includes the ability to function, and not only the absence of disease or infirmity (7). From the perspective of health promotion, the Ottawa Charter defines health as a resource that allows people to lead individual, social, and economically productive lives (8). The general practitioner Jordi Gol stated that ‘health is an autonomous, supportive, and happy way of living’ (9). Furthermore, changes in society have also implied evolution in the role of the population concerning their care and decision making about their health.

In such a framework, health promotion is the process of equipping people with the necessary means to improve their health and exercise greater control over it (10, 11). According to the World Health Promotion Conference in Shanghai (2016), three areas within health promotion need priority: (1) good governance for health, (2) the promotion of healthy cities and communities, and (3) the reinforcement of health knowledge. These areas substantially coincide with the aims of the Strategy for Health Promotion and Prevention from the Spanish National Health System (SNS): to build healthy public policies, to create environments that support health and well-being, to support the empowerment of the individual through the development of personal skills, to reinforce community action, and to reorient the health services (12).

The health and well-being of both individuals and communities depends on the combination of many factors like where we live, our environment, genetics, income and education level, and family and social relationships. Notably, the access to and use of health care services have a limited impact; 80% of determinants of health are outside the influence of the health system (13).

These factors or determinants of health have been analyzed using various models. The Dahlgren-Whitehead model is one of the most widely used (14); it presents the main determinants of health as a range of concentric hierarchical layers where each layer determines the successive layers towards the center. Individuals are located in the center, with their non-modifiable characteristics such as age, sex, and genetic load. Around them, there are various layers of influences over health, such as lifestyles, social and community networks, living and working conditions, and socioeconomic, cultural and environmental conditions. Those factors that enhance the capacity of individuals to maintain health and well-being are defined as “Health Assets” according to the theory of salutogenesis (15). According to Marmot, control over one’s life and opportunities for full social participation are crucial aspects for health, well-being, and longevity (16).

Despite the endorsement of certain elements to improve the future well-being of the population (participation in the decision-making processes, the way people experience and cope with the diseases; and the ability to self-manage their own health and care), little is known about the role of personal determinants and individual aptitudes on the capacity to adopt health-promoting behaviors and respond appropriately to adverse situations. Several classic health-related behavior models and theories and the more recent integrative frameworks try to explain human behavior, the most widely used being the Theoretical Domains Framework (TDF) (17). This framework includes 12 domains derived from 33 theories and covers the main factors that influence behavior, namely knowledge, skills, social/professional role and identity, beliefs about capacities and consequences, memory, attention and decision processes, and social influences. Nevertheless, population-based studies on the predictive validity of the behavioral frameworks applied to health and well-being are lacking.

The importance of the development of personal aptitudes is stated in the Ottawa Charter (8) as one of the bases for establishing health public policies. The efforts to attain such a development should be directed towards providing information and health education and improving the abilities essential for life. This, in turn, would increase the options available for the population so they could exercise higher control over their health and the environment that influences it (8). The evaluation of personality traits includes a whole set of psychological and behavioral characteristics and the internal organization, which make different persons act differently when facing a similar circumstance (18). Certain personality traits are related to harmful behaviors, physical and mental health problems, lower longevity, and more mortality from all causes (19–23).

Some personal aptitudes stand out among those with higher potential impact on health improvement, quality of life, or reduced use of health services: personality traits, locus of control (LOC), self-efficacy, resilience, activation, and health literacy.

The locus of control (LOC) is defined as the extent to which individuals hold agency regarding the events that occur in their life. It can be internal—when the individuals believe that events in their lives are due to their own actions, attitudes, or behaviors; or external—when people believe it is the result of luck, chance, destiny, or the decisions of others (24). The presence of an internal LOC has been associated with a better perception of general health, a lower perceived burden of the diseases (25, 26), and a positive attitude towards health promotion and primary prevention activities (27). Regarding the workplace, the presence of an internal LOC is associated with higher job satisfaction and well-being, better job performance, and lower levels of stress (28). An external LOC has been associated with a worse health status (29), more use of the emergency services and hospital admissions (30), a higher risk of developing cardiovascular diseases (25) and other chronic diseases (31), and a worse physical and psychological health status (32).

Self-efficacy refers to the feeling of confidence in one’s abilities to adequately manage certain stressors in life (33). High self-efficacy was related to better mental function (34); better memory levels, speed of thought, and intelligence (35, 36); and a higher probability of acquiring healthy lifestyles (37). Low self-efficacy has been associated with anxious personality disorder (38).

Resilience is a dynamic process of positive adaptation to stress and adversity regarded as a protective factor against mental problems (39). A high degree of resilience has been considered a protective factor against mental diseases (40). Some authors have even suggested that it is a form of “mental immunity” (41). Resilience is also related to better cognitive function in older adults, specifically, greater verbal fluency and speed of perception (42).

Activation is defined as the capacity and ability to manage one’s personal condition, collaborate with the health provider to maintain one’s own health and wellbeing, access adequate and high-quality care, and prevent health deterioration (43). The Patient Activation Measure (PAM) allows evaluation of the self-knowledge, motivation, and aptitude to manage one’s own health (43). Activation is a tool that allows individuals to reach and maintain healthy lifestyles, and optimize their quality of life (44). Higher activation levels are associated with people with better self-healing capacity, better health status, and lower use of health services (45, 46).

Health literacy refers to the health knowledge of the population, their motivation and individual abilities to understand and make decisions related to the promotion and maintenance of their health (47). Adequate health literacy levels have been associated with healthy lifestyle behaviors, such as eating five servings of fruit and vegetables per day or being a non-smoker-regardless of age, educational level, sex, ethnicity, or income (48, 49). Low health literacy can hinder health self-care and be related to a higher incidence of chronic diseases (50). From a health and social perspective, the improvement of health literacy is an unavoidablechallenge.

To date, we have not identified longitudinal studies that delve into the analysis of all these personal aptitudes and their impact on health in our population. And yet, consideration of the interrelation of personal aptitudes and determinants of health is essential. Even more, there is solid evidence to support the association of socioeconomic, cultural, and environmental determinants with lifestyles, certain risk factors, and diseases (51). In the framework of the WHO 25 × 25 strategy, a recent meta-analysis of 48 cohorts that included 1.7 million people compared persons with low versus high socioeconomic status. Overall mortality rates were higher in the first group (hazard ratio, 95% confidence interval of 1.42, 1.38–1.45 in men, and 1.34, 1.28–1.39 in women), who also had those lifestyles that caused higher premature mortality (52). Other recent findings have shown that social and emotional support can protect health and well-being. However, further research should explain the reasons for this association, and understand its context and mechanisms (53). One of the most highlighted social determinants is the social capital, which refers to the resources available to individuals and groups through social networks (54, 55). Greater social capital has been associated with a better subjective perception of health and well-being (56, 57). Several observational studies indicated that higher social capital is a protective factor against mental and physical health, and mortality (58–60). Another conditioning factor is the working environment (13). Work stress has been associated with worse health status (61), increased risk of depressive disorders (62, 63), sleep disturbances (64), coronary heart disease (65), musculoskeletal pathology (66), alterations of lipid metabolism, and increased metabolic syndrome markers (67).

We believe that the analysis of the causal relationship between personal aptitudes and the adoption of healthy lifestyles, improvements in self-management of chronic conditions, quality of life, incidence and control of risk factors, incidence of chronic diseases and mortality is of special interest, and the creation of a cohort from Primary Health Care (PHC) is a most appropriate framework.

This project will contribute to provide essential knowledge for enabling and promoting the design of individualized interventions adapted to personal abilities and the evaluation of their role as prognostic factors. The interventions would also aim at improving the aptitudes that can be modified, such as health literacy, and the impact of these modifications may be assessed. Identification of the key determinants of multimorbidity is essential for the development of effective strategies for the healthcare and well-being of the person (2).

Accordingly, we propose to conduct an extensive investigation, with a holistic approach, on the determinants of health. Special focus will be given to the influence and effects of factors that determine individual behavior; a gender perspective and other aspects of social inequality will be included in the design and analysis. The description of these individual determinants involved in behaviors and their relation to social determinants, lifestyles, risk factors, chronic diseases and mortality are of paramount interest to our evolving societies and health systems.

### Study objectives and hypotheses

1.1.

This project was designed as a hybrid study, composed of a quantitative part (exposed in this article) and a qualitative part (published in another article).

The quantitative part of the DESVELA cohort has the following objectives:

To analyze whether personal aptitudes related to certain behaviors (self-efficacy, activation, health literacy, resilience, locus of control, and personality traits) are independently associated with the incidence of morbidity.To analyze whether personal aptitudes related to certain behaviors (self-efficacy, activation, health literacy, resilience, locus of control, and personality traits) are independently associated with lower all-cause mortality, improved engagement in healthy lifestyles, higher quality of life, and lower utilization of the health services during follow-up.

We hypothesize that personal aptitudes that are related to positive behaviors (a higher self-efficacy, activation, health literacy, resilience, an internal locus of control, and positive personality traits) will be independently associated with a lower incidence of morbidity. We also hypothesize that personal determinants related to positive behaviors (a higher self-efficacy, activation, health literacy, and resilience, an internal locus of control, and positive personality traits) will be independently associated with all-cause mortality, engagement in healthy lifestyles, higher quality of life, and more optimal use of the health services during follow-up.

## Materials and methods

2.

### Aim, design and study setting

2.1.

We aim to evaluate the influence of personal aptitudes on lifestyles and quality of life, the incidence of the most relevant health problems, the utilization of the health services, and all-cause mortality (Figure 1).

**Figure 1 fig1:**
[figure not shown]
Diagram showing the causal relationship proposed in the study between the independent variables (personal aptitudes), the dependent variables (morbidity, lifestyles, quality of life, use of services and mortality) and the modulating effect of the covariates.

This is a multicenter study for the creation of a prospective cohort of persons assigned to Primary Healthcare (PHC) centers within nine autonomous communities (AACC; Catalonia, the Basque Country, Castilla y León, Aragón, Galicia, the Balearic Islands, Castilla La Mancha, Andalusia and Madrid). Follow-up examinations and evaluations will be at 5 and 10 years from the entry date.

### Participants

2.2.

We will include persons aged 35–74 years assigned to the above-mentioned PHC centers, selected by random sampling. Exclusion criteria will apply to persons with a terminal condition or institutionalized at the time of recruitment; persons with intellectual disabilities, dementia, or language difficulties; and persons who plan to move out of Spain within 5 years from study initiation.

### Sample size

2.3.

The sample size was computed using the GRANMO sample size calculator. We considered the estimation of the relative risk (RR) for a cohort study (using the Poisson approximation), with 10 years of follow-up and a rate of loss to follow-up of 30%, accepting an alpha risk of 0.05 and a beta risk of 0.2 in a bilateral contrast. The incidence of morbidity was considered as the main dependent variable and was around 60% in a previous analysis with 10.14 years follow-up (2). Health literacy was considered as the main independent variable. According to the questionnaire HLS-EU, 58,3% of the Spanish population has an inadequate or problematic level of health literacy (47). Low levels of health literacy have been linked to poorer physical and mental health outcomes, increased use of health services (68–70), and higher all-cause mortality (71, 72). Taking all these parameters into account, a sample of 3,083 persons is required, 1,793 in the exposed group (inadequate or problematic health literacy, HLS-EU-Q16 score between 0 and 12) and 1,290 in the non-exposed group (HLS-EU-Q16 score between 13 and 16). The sample size has been calculated to detect a minimum RR of 1.1 at 10 years, and will allow the detection of a minimum RR of 1.2 at 5 years, which is lower than some of the figures reported in the literature (73).

### Variables

2.4.

All the questionnaires used in the study are validated in Spanish except for the LOC, which will be assessed by a single question not yet validated. Table 1 shows the name of the questionnaire, the number of items, and the citation.

**Table 1 tab1:** Validated questionnaires used in the study.

Optional self-administration in our study	Questionnaires	Number of items	Reference of validated version in Spanish
	*Independent variables* *(Personal aptitudes)*		
Yes	Sherer’s general self-efficacy scale (GSES-12)	12	(74)
No	Patient Activation Measure (PAM)	13	(46)
Yes	10-item Connor-Davidson Scale	10	(75)
No	Health Literacy (HLS-EU-Q16)	16	(76)
No	10-Item Big Five Inventory (BFI-10)	10	(77)
	*Covariables*		
Yes	Functional social support (Duke-UNC-11)	11	(78)
Yes	WHO Disability Assessment Schedule (WHODAS 2.0)	12	(79)
Yes	List of Threatening Events (LTE)	12	(80)
Yes	Effort-Reward Imbalance questionnaire (DER/ERI)	16	(81)
	*Dependent variables*		
No	Adherence to the Mediterranean diet (Predimed and Predimed Plus)	23	(82, 83)
Yes	International Physical Activity Questionnaire (IPAQ)	4	(84)
Yes	Pittsburgh Sleep Quality Index (PSQI)	11	(85)
Yes	Quality of Life (EuroQol 5D–5 L)	5	(86)
No	Generalized anxiety disorder (GAD-7)	7	(87)
No	Depression Test Questionnaire (PHQ-9)	9	(88)
No	Depression Risk Calculator (PredictD)	2 + 12	(89)

The independent variables in this study refer to personal aptitudes, will be measured at baseline, and are listed as follows with the corresponding measurement tools: self-efficacy, which will be measured with the Sherer’s general self-efficacy scale (74); activation, measured with the Patient Activation Questionnaire (PAM) (46); resilience, measured with the abbreviated version of the 10-item Connor-Davidson scale (75); health literacy, evaluated with the HLS-EU-Q16 literacy questionnaire (76); LOC, assessed with the statement “I feel that events in my life are often determined by factors that are beyond my control” which has 6 response options in a Likert-type scale; personality characteristics will be examined using the 10-Item Big Five Inventory (BFI-10) for determination of personality traits (77).

The dependent variables in this study are morbidity, all-cause mortality, adoption of healthy lifestyles, quality of life, and utilization of health services. The information regarding the main dependent variables will be recorded at baseline and during the follow-ups at 5 and 10 years through surveys, physical examination and review of the medical records. The presence of morbidities will be assessed through the diagnoses in the medical records and physical examination. The medical records will also be the source to assess all-cause mortality.

Regarding the physical examination, blood pressure of participants will be measured and hypertension defined following the recommendations and criteria of the Spanish Hypertension Society. The ankle-brachial index (ABI) will be measured with a Vasera device (Fukuda Denshi), and peripheral arterial disease considered when ABI < 0.9. Weight and height will be measured to obtain the body mass index (BMI), and overweight and obesity will be considered if 25 ≤ BMI < 30 and BMI > 30, respectively. Waist circumference will also be measured. Blood testing will be performed to measure fasting glucose levels, glycated hemoglobin (HbA1c), total, low and high-density lipoprotein cholesterol, triglycerides, and creatinine.

For each participant, morbidity will be recorded at baseline and during follow-up by considering all the active conditions in the medical records at the time of the visit. We will define incident morbidity as the onset of any of the following 17 group conditions, provided they are not present at baseline: hypertension, ischemic heart disease (angina or acute myocardial infarction), heart failure, cardiac arrhythmias, diabetes mellitus, ischemic stroke, peripheral arterial disease, chronic obstructive pulmonary disease, asthma, any type of arthritis, osteoporosis, any type of cancer, Parkinson’s disease, one or more affective disorders (depression, anxiety), one or more psychotic disorders (schizophrenia, psychosis, bipolar disorder), dementia (including Alzheimer’s disease), and obesity. If we detect any frequent condition at follow-up that has not already been included in these 17 proposed groups, we will add a new group category.

The evaluation of the participants’ mental health will also include the following: a questionnaire on the generalized anxiety disorder (GAD-7) (87), which evaluates the presence of symptoms; examination of the diagnostic criteria for major depression, using the PHQ-9 (88); and estimation of the risk of depression (89), in participants with no diagnosis of a major depressive episode.

We will evaluate the several lifestyles: adherence to the Mediterranean diet, assessed with the PREDIMED (82) and PREDIMED plus (83) questionnaires; type of diet, determined by asking the participants if they follow any specific diet (e.g., vegetarian, vegan); level of physical activity, assessed with the International Physical Activity Questionnaire (84); smoking habit, measured with the 4-question scale adapted from the WHO MONICA study (90); alcohol consumption, considering the total units during the past week and a question on the monthly frequency of excessive consumption (binge drinking) over the past year; and sleep, evaluated using the Pittsburgh Sleep Quality Index (85), the overall number of sleeping hours, usual bedtime, and waking-up time.

The quality of life will be determined using the EUROQol 5D-5L health questionnaire (86), and a question on self-perceived well-being. Finally, the utilization of health services for the last 12 months previous to inclusion into the study will be extracted from electronic health records. Where the research team may have no access to electronic health records, the utilization of health services will be assessed with a survey answered by the participants. The items will enquire on the number of visits (to the emergency department, primary care, and other specialties), hospital admissions, diagnostic tests, and pharmacological treatment (medication, dose, total daily dose, and duration).

Additionally, we will consider the following groups of covariates: sociodemographic, social, functional capacity, and stress level.

We will register the following sociodemographic variables: date of birth, sex, sex orientation, and gender identity (SOGI questions), marital status, nationality, and employment status. We will also consider occupational social class, defined with the educational level and occupation. Participants will answer questions on employment conditions (six items), domestic and care work (six items), income level and economic situation (four items), and housing and material situation.

The two social variables included in this study are the social capital and the functional social support questionnaire. To assess the social capital, we will use the harmonized questionnaire proposed by Blaxter et al. (91) where five dimensions are identified: perspectives about the local area, civic engagement, social and support networks, social participation, and reciprocity and trust (91, 92). To assess the functional social support we will use the validated Spanish version of DUKE-UNC-11 (78). The questionnaire evaluates two sub-scales: confidential support (7 items) and affective support (4 items).

The functional capacity of participants will be evaluated using the WHO Disability Assessment Schedule (WHODAS 2.0) (79), a 12-item self-administered questionnaire.

The stress level will be assessed by taking into account stressful life events, using the List of Threatening Experiences questionnaire (80); and also occupational stress, determined in employed persons at the time of recruitment using the Effort-Reward Imbalance questionnaire (81). There will also be five questions regarding the impact of COVID-19.

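### Most condition groups in the primary outcome depend on a recorded diagnosis, while the aptitudes are expected to change service use, so differential recording can create or hide an RR of 1.1

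*Protocol article*

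**What the plan says.** Incident morbidity, the main dependent variable, is the onset of any of 17 condition groups absent at baseline (Variables). On its source the article says: "The presence of morbidities will be assessed through the diagnoses in the medical records and physical examination". A later sentence in the same section, on how morbidity is recorded for each participant, mentions only conditions active in the medical record.

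The section gives a visit-based criterion for three groups: hypertension (measured blood pressure), peripheral arterial disease (ankle-brachial index) and obesity (BMI). Fasting glucose, HbA1c, PHQ-9 and GAD-7 are also collected, but no rule turns their results into outcome events. A cognitive evaluation is named only in the Abstract.

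On service use, the second objective looks for "lower utilization of the health services during follow-up" in people with the favourable aptitudes. The Introduction says of activation: "Higher activation levels are associated with people with better self-healing capacity, better health status, and lower use of health services". It links external locus of control to "more use of the emergency services and hospital admissions". The Sample size section links low health literacy, its main exposure, to greater service use.

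The Statistical analysis section plans one Cox model per aptitude. Service use is not among the named covariates, and the only named sensitivity analyses concern loss to follow-up. Study limitations does not mention ascertainment.

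**The concern.** A diagnosis enters the record only after the person has contact with a clinician who codes it. If people with favourable aptitudes consult less, some of their arthritis, anxiety, osteoporosis or asthma may stay unrecorded, and their recorded incidence falls without any difference in disease. That is the direction of the primary hypothesis.

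The target effect is small, so a modest difference in recording matters. A positive result for the first objective could then partly restate a difference in service use, which the second objective examines separately. Where an aptitude leads to more preventive contact, the same mechanism would add recorded diagnoses in the favourable group and could hide a real benefit.

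**Working it through.** **1. Count of groups (Variables).** Three of 17 groups have a stated visit criterion, leaving 17 − 3 = 14 (82%) that need a recorded diagnosis. Treating diabetes (glucose, HbA1c), affective disorders (PHQ-9, GAD-7) and dementia (cognitive evaluation) as study-measured leaves 14 − 3 = 11 (65%). These are counts of condition groups. The article gives no breakdown of events.

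**2. The plan's own figure.** Inputs from Sample size:
- error rates: "accepting an alpha risk of 0.05 and a beta risk of 0.2 in a bilateral contrast"
- incidence: "was around 60% in a previous analysis with 10.14 years follow-up"
- effect: "The sample size has been calculated to detect a minimum RR of 1.1 at 10 years"
- 1,793 exposed, 1,290 non-exposed, 30% loss

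A continuity-corrected comparison of two proportions, 0.66 against 0.60, with allocation 1,290/1,793, gives 1,250 exposed and about 2,149 in total. Then 2,149/0.70 ≈ 3,070, within 0.4% of the stated 3,083. The design target can therefore be read as 66% against 60%.

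**3. Bias under no true effect, deficit across the whole composite.** Let the low-aptitude risk be 0.60. Let conditions in the high-aptitude group be recorded at a relative rate k, which is an assumption because the article gives no such figure. The recorded risk in the high-aptitude group is 1 − 0.4^k, so RR = 0.60/(1 − 0.4^k).

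| Recording deficit | k | 1 − 0.4^k | RR |
|---|---|---|---|
| 5% | 0.95 | 0.581 | 1.03 |
| 10% | 0.90 | 0.562 | 1.07 |
| 15% | 0.85 | 0.541 | 1.11 |
| 20% | 0.80 | 0.520 | 1.15 |

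**4. The same, with part of the composite immune.** Suppose half the event rate is found by study examination whatever the consulting habit (also an assumption). Then k = 0.5 + 0.5 × (1 − deficit).
- 10% deficit: k = 0.95, RR = 1.03
- 15% deficit: k = 0.925, RR = 0.60/0.572 = 1.05

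**5. What would reproduce the design target.** Work now with the share of affected people captured by the end of follow-up, which is a different scale from the rate in steps 3 and 4. Assume full capture in the low-aptitude group. RR = 1/(f + (1 − f)s), where f is the share of events found by examination and s is the relative capture of the rest. Setting RR = 1.1 gives s = (1/1.1 − f)/(1 − f).

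| f | s needed | Shortfall |
|---|---|---|
| 0 | 0.909 | 9% |
| 0.3 | 0.870 | 13% |
| 0.5 | 0.818 | 18% |
| 0.6 | 0.773 | 23% |

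**6. Chance of a false positive.** After 30% loss, 1,255 exposed and 903 non-exposed remain. With 60% recorded incidence in the low-aptitude group and no true effect, the chance of p < 0.05 in the hypothesised direction is about 29% at overall relative capture 0.95 and 72% at 0.909. The nominal figure in that direction is 2.5%.

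**The case against.** The strongest reply has four parts.

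- **Labels are not events.** Hypertension and obesity may supply a large share of events and are measured at the visit. Myocardial infarction, stroke and cancer are unlikely to go unrecorded. This stands. It shrinks the bias (step 4) without removing it, and it means the group count cannot be read as a share of events.
- **The direction is not uniform.** The hypothesis speaks of more optimal use, not simply less. Internal locus of control is linked to a favourable attitude to prevention, and activation is defined partly as being able to obtain good care. This stands too, so the concern is bias in either direction.
- **Lower use may follow from better health.** It may, and the documents cannot separate the two. For the same reason, adjusting for service use during follow-up is not a safe remedy.
- **Examination results are sent to participants** (Data collection process), which may even out recording. This helps only for measured conditions.

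A reader might infer that the study has no outcome independent of consulting. The documents do not support that: all-cause mortality has its own analysis, and quality of life, diet, physical activity, sleep, PHQ-9 and GAD-7 come directly from participants. A reader might also infer that under-diagnosis will produce the hypothesised result. The documents give no capture figures and no event breakdown, so only the possibility is established.

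A sensitivity analysis might be left to a fuller document. The primary outcome definition, however, is fixed in this article, and the dependence on records arises there.

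**Conclusion.** The concern holds in a limited form. Between 11 and 14 of the 17 condition groups depend on a recorded diagnosis, the protocol expects the exposures to alter service use, and no stated analysis of the primary outcome distinguishes recording from disease. Differential recording can therefore create, or for some aptitudes hide, an association of the size targeted.

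Under assumed deficits of 10-15% in recording rate, the spurious RR is 1.07-1.11 if the whole composite is affected. It is about 1.03-1.05 if half the event rate is found by examination. All of these rest on no true effect, 60% risk in the low-aptitude group, and deficits and examination shares that the documents do not supply.

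**What to change.** In Variables (2.4) and Statistical analysis (2.6):

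1. State that visit measurements already in the protocol (blood pressure, ankle-brachial index, BMI, glucose/HbA1c, PHQ-9, GAD-7) count as outcome events by pre-specified criteria, applied identically at baseline, 5 and 10 years.
2. Add one pre-specified sensitivity outcome limited to the conditions so measured plus events unlikely to go unrecorded (myocardial infarction, stroke, cancer).
3. For each aptitude, report its hazard ratio and confidence interval beside the 17-group result. If the association is materially attenuated in the sensitivity outcome, describe the 17-group result as recorded morbidity.

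Agreement in direction alone is too weak a test, since a noisy outcome with no true effect agrees about half the time. Adjustment for follow-up service use should not be relied on either, because that use may itself result from better health.

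The cost is one extra outcome definition and one extra model per aptitude. The article already plans examination, surveys and record review at 5 and 10 years, though the listed measurements must actually be repeated then. The downsides are fewer events, wider intervals, and visit-based conditions seen only in attenders.
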